### Participants

2.3

#### Recruitment and informed consent

2.3.1

Participants will be recruited from the outpatient and inpatient departments of the Affiliated Hospital of Chengdu University of Traditional Chinese Medicine, Chongqing Hospital of Traditional Chinese Medicine, Chengdu Shuangliu District Hospital of Traditional Chinese Medicine, and Chengdu Longquanyi Hospital of Traditional Chinese Medicine. Recruitment is scheduled to commence on July 1, 2025. Investigators will strictly adhere to the inclusion and exclusion criteria to determine each individual’s eligibility for the study.

All potential participants will be informed of the study’s purpose and nature, and provided with comprehensive information about the research, including its procedures, potential benefits, and risks. Before enrollment, they will voluntarily sign an informed consent form (Supplementary File 2). Participants reserve the right to withdraw from the study at any time without penalty or loss of benefits, and are not required to provide a reason for withdrawal. Any reasons for withdrawal, if provided, will be documented.

#### Inclusion criteria

2.3.2

According to the Bárány Society (2), vascular vertigo can result from either central lesions (brainstem, cerebellar, or supratentorial) or isolated labyrinthine infarction/hemorrhage. In the present study, only patients with central vascular vertigo following ischemic or hemorrhagic stroke are eligible.

Inclusion requires: (1) neuroimaging evidence of a lesion involving the vertebrobasilar territory or supratentorial central vestibular structures (e.g., brainstem, cerebellum, thalamus, insula, temporo-parietal cortex) that is judged by the investigator to be responsible for the vertigo; (2) aged 30–80 years (inclusive), regardless of gender; (3) ≥ 2 weeks since the onset of cerebral infarction or cerebral hemorrhage, with persistent vertigo or postural instability for ≥1 week (vertigo-related symptoms must not precede the diagnosis of cerebral infarction/hemorrhage); (4) Barthel Index (BI) score >40; (5) stable vital signs and overall clinical condition; ability to complete a vertigo diary as instructed; (6) not participating in any other trials during the study period and signing a written informed consent form.

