#### Exclusion criteria

2.3.3

Participants will be excluded from this study if they meet any of the following criteria: (1) other primary peripheral vestibular disorders (e.g., Ménière disease, vestibular neuritis, benign paroxysmal positional vertigo), including isolated vascular events affecting solely the peripheral vestibular apparatus (e.g., labyrinthine infarction/hemorrhage) with no concomitant central nervous system involvement; (2) they have vascular vertigo associated with vertebral artery compression syndrome; (3) vertigo caused by non-vascular factors (e.g., intracranial space-occupying lesions, otogenic diseases, metabolic/infectious diseases, trauma) confirmed by examination; (4) they have comorbid severe primary diseases involving the cardiovascular system, liver, kidneys, digestive system, hematopoietic system, or other major organ systems; (5) they have been diagnosed with other central nervous system diseases within the past 6 months; (6) there are severe skin lesions or skin diseases at the treatment site; (7) they have coagulation disorders or hemorrhagic diseases; (8) pregnant, lactating, or females planning pregnancy within 6 months; (9) they are unable to understand the content of the vertigo diary or complete the required recordings; (10) they are in a comatose state or have consciousness disorders; (11) they are unable to cooperate with all study procedures due to mental illness, cognitive impairment, or emotional disorders; (12) current participation in another clinical trial or participation in one within the past 3 months.

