### Baseline characterization and lesion documentation

2.4

For all enrolled patients, the location of the responsible lesion will be documented based on the qualifying MRI or CT scan. Lesion location will be classified *a priori* into three categories: (1) brainstem lesions; (2) cerebellar lesions; and (3) supratentorial central vestibular lesions (e.g., thalamic, temporo-parietal, insular). In cases with combined lesions, the predominant clinically relevant site will be recorded. The distribution of patients across these lesion categories will be summarized in the baseline characteristics table. This categorization will also serve as a basis for exploratory subgroup analyses to investigate potential differential treatment responses based on neuroanatomical substrate.

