### Sample size

2.5

The sample size was calculated on the basis of the primary outcome, change in total DHI score. The assumed mean DHI scores were derived from a previous randomized trial on vestibular vertigo (20) and supported by a pilot study of 30 PSVV patients conducted by our team prior to this trial. The pilot data indicated a mean DHI reduction of approximately 12 points in the acupuncture group compared to sham, which informed our assumed group differences. On thess evidence, this study assumes that the mean Dizziness Handicap Inventory (DHI) score will be 21 in the acupuncture group for post-stroke vascular vertigo, 33 in the sham acupuncture group, and 30 in the active drug group, with a predefined standard deviation (SD) of 20. Sample size calculation will be performed using PASS software, with a set power (1-*β*) of 0.90 and a significance level (*α*) of 0.05. Following this calculation, a minimum of 66 participants will be required for each group, yielding a total sample size of 198; considering a 15% attrition rate, the total sample size will be adjusted to 234, with no fewer than 78 participants in each group.

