### Randomization and blinding

2.6

All eligible participants will be randomly assigned to three groups at a 1:1:1 ratio using computer-generated random numbers sealed in opaque envelopes. Dedicated personnel responsible for randomization will open the envelopes in enrollment order and inform treating physicians of group assignments. All steps in the implementation of this trial’s randomization protocol will be conducted by dedicated randomization staff who are not involved in the trial itself. Blinding of the acupuncture practitioners will not be feasible due to the nature of the interventions. Nevertheless, the principle of blinding will be consistently upheld throughout the trial: participants in the acupuncture group and sham acupuncture group will receive treatment in separate, partitioned rooms to prevent interaction with other groups. After the 3-week treatment period, a blinding assessment will be conducted for these two groups to evaluate the perceived treatment type (real acupuncture, sham acupuncture, or undetermined) based on participants’ experience. Throughout the trial, the principle of separating researchers, operators, and statisticians will be strictly followed.

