#### Clinical data analysis

2.10.1

Clinical outcomes will be analyzed using SPSS 23.0 statistical software, with a significance level of *p*-value < 0.05. All analyses will be performed by independent statisticians blinded to group assignments and interventions. Two core analysis sets will be used: (1) Full Analysis Set (FAS): All randomly assigned participants who received at least one treatment session. Missing values for primary outcomes will be imputed using the Last Observation Carried Forward (LOCF) method, and FAS results will be the primary analytical basis. (2) Per Protocol Set (PPS): Participants with no exclusion criterion violations, ≥10 completed acupuncture sessions, and at least the Week 3 assessment. PPS results will serve as supplementary references. Relevant statistical analyses will also cover case distribution analysis, which will calculate the sample size of each analysis set per group, case distribution across study centers, and total numbers of dropouts and withdrawals (with respective reasons), and present these data in detailed tables.

The correlation between baseline treatment expectation and changes in DHI will be examined using Pearson correlation. In addition, multiple linear regression models will be constructed with change in DHI as the dependent variable, and baseline expectation score, treatment group, baseline DHI, age, and sex as independent variables, to examine whether expectation independently predicts treatment response. Exploratory interaction terms between treatment group and expectation will be tested to evaluate whether the magnitude of the acupuncture effect differs according to baseline expectation level.

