To ensure reliable results, participants will be randomly assigned to groups, with outcome assessors and statisticians blinded to group assignments to minimize potential bias. However, this trial has several limitations. Owing to the inability to blind among the acupuncturists, the use of self-reported outcomes, and the potential placebo effect of acupuncture, the study results may be prone to bias. Additionally, a challenge for clinical applications of rs-fMRI is the potentially confounding effect of concomitant vascular diseases, aging, or medication on the neurovascular coupling and consequently the fMRI imaging response (33). Therefore, quality control methods are prerequisites for reliable results: (1) recruit right-handed patients for MRI to avoid dominant hand effects on brain structure and function; (2) acupuncture procedures will be strictly performed by trained, certified practitioners with at least 3 years of experience following standardized protocols; (3) Standardized, highly repeatable acupuncture interventions; (4) participants will be instructed to maintain their usual lifestyle for 24 h before scanning, avoiding late nights, smoking, and consumption of coffee or tea. During scanning, participants will close their eyes and wear earplugs. Following the scan, participants will document sensations experienced during the procedure, including somatic sensations, psychological state, and thought activity, to explore the influence of various factors on test outcomes.

In summary, this trial will evaluate the efficacy of acupuncture for PSVV and explore its central mechanisms. It will provide evidence for acupuncture’s effectiveness in treating PSVV and preliminarily investigate its neuroplasticity effects. Additionally, quality control methods will be implemented to enhance the reliability of results. We anticipate this study will offer guidance for the early treatment of PSVV. Findings will be reported according to the Consolidated Standards of Reporting Trials (STRICTA) guidelines (34).

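### Time since stroke has no upper limit at entry and enters no stated analysis, so the expectation and imaging associations may reflect stage of recovery and nothing isolates the early patients the Discussion refers to

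*Protocol article*

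**What the plan says.** Inclusion criterion 3 (section 2.3.2) requires "≥ 2 weeks since the onset of cerebral infarction or cerebral hemorrhage", "with persistent vertigo or postural instability for ≥1 week". Both periods have a floor and neither has a ceiling. The only time window on neurological history in the Exclusion criteria (2.3.3) is "they have been diagnosed with other central nervous system diseases within the past 6 months", which concerns other diseases and does not cap time since the index stroke.

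Time since stroke is not mentioned again where the article describes its analyses:

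- Clinical data analysis (2.10.1) gives one regression of DHI change, with "baseline expectation score, treatment group, baseline DHI, age, and sex as independent variables". Its stated purpose is to see whether expectation predicts response independently. Exploratory group-by-expectation interactions are added.
- DTI data (2.10.2.3) correlates FA before and after treatment with DHI change, to explore whether acupuncture works through white matter integrity. It then adds Pearson correlations between clinical and fMRI results. No adjustment is described.
- Baseline characterization (2.4) classifies lesion site and says "This categorization will also serve as a basis for exploratory subgroup analyses". No other clinical subgroup factor is named.

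The closing paragraph of the Discussion states: "We anticipate this study will offer guidance for the early treatment of PSVV".

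**The concern.** A patient a little over two weeks from the stroke and a patient years from it can both enter. If the two differ in how much they would improve without study treatment, stage of recovery becomes a source of variation in DHI change. It may also move the imaging measures. The article itself links network abnormality and recovery to recovery after stroke, and links those abnormalities to white matter damage (rs-fMRI data, 2.10.2.2).

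Two things are at stake. First, the expectation regression and the imaging correlations relate one patient characteristic or change to another. Neither expectation nor FA change is randomised, so a shared dependence on stage of recovery could produce an association that is then read as an effect of expectation or as a mechanism of acupuncture. Mechanism is one of the trial's two primary objectives (2.1). Second, a result in a mixed population could be cited for early treatment even if late patients mainly produced it, and no stated analysis would show this.

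**Working it through.** **1. The plan's own figure.** Inputs from Sample size (2.5): means "21 in the acupuncture group for post-stroke vascular vertigo, 33 in the sham acupuncture group, and 30 in the active drug group", SD 20, power 0.90, alpha 0.05, attrition 15%. The grand mean is 28, the deviations are −7, 5 and 2, and their squares sum to 49 + 25 + 4 = 78. For a one-way ANOVA F test the noncentrality at 66 per group is 66 × 78 / 400 = 12.87. Power is 0.8957 at 65 per group and 0.9005 at 66, so 66 is reproduced. Then 66 / 0.85 = 77.6, rounded up to 78, and 3 × 78 = 234. The sample size stands.

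**2. Precision of the arm contrasts.** Assumptions, none from the article: half the patients are early and half late; their mean DHI change differs by d = 5, 10 or 15 points; the SD of 20 already contains this spread and applies to DHI change. The variance due to stage is 0.5 × 0.5 × d².

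| d | Variance due to stage | Share of 400 | SE of a pairwise contrast after adjustment |
|---|---|---|---|
| 5 | 6.25 | 1.6% | 3.18 |
| 10 | 25 | 6.3% | 3.10 |
| 15 | 56.25 | 14.1% | 2.97 |

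The unadjusted SE at 78 per arm is 20 × √(2/78) = 3.20, and the last column is 3.20 × √(1 − share). The gain is modest.

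**3. Chance imbalance is the same quantity.** Under simple randomisation the between-arm difference in the early share has SD √(2 × 0.25 / 78) = 0.080. Multiplying by 1.96 × d gives ±0.8, ±1.6 and ±2.4 points. At d = 10 the variance ratio is 0.80² / 3.20² = 6.25%, exactly the share in the table. This is a component of the ordinary sampling error (±1.96 × 3.20 = ±6.3 points), already covered by the confidence interval. It must not be counted as a second harm.

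**4. The associations that are not randomised.** If two measures are unrelated within each stage but both differ by stage, their correlation in the mixed sample is r(stage, DHI change) × r(stage, other measure). In a 50:50 mix the first factor is 0.5 × d / 20 = 0.125, 0.25 or 0.375 for d = 5, 10 or 15. The second is unknown. If it is as large as the first, the induced correlation is 0.016, 0.063 or 0.141; it can never exceed the first factor. This shows the mechanism and a possible range. It is not an estimate for this trial.

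**5. Early treatment.** Set side by side, the entry criterion has a floor only, lesion site is the one named subgroup factor, and the Discussion speaks of early treatment without defining it. No stated step connects them.

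**The case against.** The strongest reply is that all three arms are randomised concurrently, so spontaneous recovery occurs in each and cancels on average. That is correct. A reader might infer that mixing recovery stages biases the efficacy comparison; the design does not support that inference.

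A second reply is that the covariate list quoted from 2.10.1 belongs to the expectation model. That is also correct. It should not be read as the adjustment set for the primary efficacy analysis, which the article does not give. Section 2.4 likewise does not say that lesion site is the only subgroup. Randomisation is described as "randomly assigned to three groups at a 1:1:1 ratio using computer-generated random numbers sealed in opaque envelopes" with no stratification factor, but an article may leave that, and the primary model, to a fuller document. None of these silences is counted here.

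Third, broad entry is deliberate: the Discussion says that the study widens the population. The early-treatment remark is one anticipatory sentence, not an objective, and patients from week 2 are eligible. So it would be too strong to say that the trial cannot inform early treatment. If mostly early patients were recruited, the data might.

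Fourth, the size of any early-late difference is unknown. That also stands, which is why only ranges are shown.

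What these replies leave untouched is the content that the article does fix: a regression with a listed covariate set, correlations described without adjustment, and a sentence about early treatment with no analysis behind it.

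**Conclusion.** The point holds in a limited form. For the randomised contrasts there is no bias on average and no error in the sample size. Adjusting for time since stroke would remove about 2 to 14% of the variance under the stated assumptions (50:50 mix, gap of 5 to 15 DHI points, SD of 20 inclusive of that spread). A reader might go further and infer lost power. That would require the SD of 20 to apply within a recovery stage, in which case power at 66 per group would be 0.896, 0.881 or 0.856 for gaps of 5, 10 or 15 points. The article does not say this, and the loss is not claimed.

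The substantive part is elsewhere. The expectation regression and the FA and fMRI correlations with clinical change can be confounded by stage of recovery, and the stated analyses do nothing about it. The size cannot be fixed from the article. The sentence on early treatment has no stated analysis that isolates early patients, so it and the open-ended entry criterion need to be reconciled. The change should be made because it is nearly free; the main comparison is not at risk without it.

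**What to change.** - Derive time from stroke onset to randomisation for every patient, using the onset information that inclusion criterion 3 already requires, and report its distribution by arm.
- Add it, for example as log days, to the regression of DHI change in 2.10.1.
- In 2.10.2.3, replace the plain Pearson correlations with partial correlations or regressions adjusted for time since stroke and treatment group.
- Name it beside lesion site in 2.4 as a pre-specified exploratory subgroup, with any early/late cut fixed before unblinding.
- In the Discussion, delete the word early or limit the sentence to what that subgroup shows.

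The cost is one degree of freedom in each model, one more exploratory subgroup with the usual caution about multiplicity, and a small edit to the text. For patients far from their stroke the onset date may be approximate, which a log scale tolerates. No extra patients or visits are needed, and eligibility and clinical rules do not change.

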#### Exclusion criteria

2.3.3

Participants will be excluded from this study if they meet any of the following criteria: (1) other primary peripheral vestibular disorders (e.g., Ménière disease, vestibular neuritis, benign paroxysmal positional vertigo), including isolated vascular events affecting solely the peripheral vestibular apparatus (e.g., labyrinthine infarction/hemorrhage) with no concomitant central nervous system involvement; (2) they have vascular vertigo associated with vertebral artery compression syndrome; (3) vertigo caused by non-vascular factors (e.g., intracranial space-occupying lesions, otogenic diseases, metabolic/infectious diseases, trauma) confirmed by examination; (4) they have comorbid severe primary diseases involving the cardiovascular system, liver, kidneys, digestive system, hematopoietic system, or other major organ systems; (5) they have been diagnosed with other central nervous system diseases within the past 6 months; (6) there are severe skin lesions or skin diseases at the treatment site; (7) they have coagulation disorders or hemorrhagic diseases; (8) pregnant, lactating, or females planning pregnancy within 6 months; (9) they are unable to understand the content of the vertigo diary or complete the required recordings; (10) they are in a comatose state or have consciousness disorders; (11) they are unable to cooperate with all study procedures due to mental illness, cognitive impairment, or emotional disorders; (12) current participation in another clinical trial or participation in one within the past 3 months.

### Baseline characterization and lesion documentation

2.4

For all enrolled patients, the location of the responsible lesion will be documented based on the qualifying MRI or CT scan. Lesion location will be classified *a priori* into three categories: (1) brainstem lesions; (2) cerebellar lesions; and (3) supratentorial central vestibular lesions (e.g., thalamic, temporo-parietal, insular). In cases with combined lesions, the predominant clinically relevant site will be recorded. The distribution of patients across these lesion categories will be summarized in the baseline characteristics table. This categorization will also serve as a basis for exploratory subgroup analyses to investigate potential differential treatment responses based on neuroanatomical substrate.

### Sample size

2.5

The sample size was calculated on the basis of the primary outcome, change in total DHI score. The assumed mean DHI scores were derived from a previous randomized trial on vestibular vertigo (20) and supported by a pilot study of 30 PSVV patients conducted by our team prior to this trial. The pilot data indicated a mean DHI reduction of approximately 12 points in the acupuncture group compared to sham, which informed our assumed group differences. On thess evidence, this study assumes that the mean Dizziness Handicap Inventory (DHI) score will be 21 in the acupuncture group for post-stroke vascular vertigo, 33 in the sham acupuncture group, and 30 in the active drug group, with a predefined standard deviation (SD) of 20. Sample size calculation will be performed using PASS software, with a set power (1-*β*) of 0.90 and a significance level (*α*) of 0.05. Following this calculation, a minimum of 66 participants will be required for each group, yielding a total sample size of 198; considering a 15% attrition rate, the total sample size will be adjusted to 234, with no fewer than 78 participants in each group.

### Randomization and blinding

2.6

All eligible participants will be randomly assigned to three groups at a 1:1:1 ratio using computer-generated random numbers sealed in opaque envelopes. Dedicated personnel responsible for randomization will open the envelopes in enrollment order and inform treating physicians of group assignments. All steps in the implementation of this trial’s randomization protocol will be conducted by dedicated randomization staff who are not involved in the trial itself. Blinding of the acupuncture practitioners will not be feasible due to the nature of the interventions. Nevertheless, the principle of blinding will be consistently upheld throughout the trial: participants in the acupuncture group and sham acupuncture group will receive treatment in separate, partitioned rooms to prevent interaction with other groups. After the 3-week treatment period, a blinding assessment will be conducted for these two groups to evaluate the perceived treatment type (real acupuncture, sham acupuncture, or undetermined) based on participants’ experience. Throughout the trial, the principle of separating researchers, operators, and statisticians will be strictly followed.

